#### Study Assessments

Assessments were performed at 2 time points: 3 months following dispensing of the initial opioid prescription and 9 months following dispensing of the initial opioid prescription.

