#### Timeline for Establishing Consortium to Study Opioid Risks and Trends Criteria for Opioid Use

The timeline of the study was governed, in part, by the temporal requirements for applying CONSORT criteria (Figure 2). The beginning date of an episode of opioid use was defined as the date that the initial prescription was issued, with no previous opioid prescriptions issued for the preceding 6-month time period. The end date of an episode was the date that the last dispensed medication supply was exhausted, based on the days of supply as documented in the prescription instructions with no opioid dispensing in the ensuing 6 months. Patients who continued to use opioids on day 90 following issuance of the initial opioid prescription were invited to participate in the study assessment. Although it was not possible to accurately apply CONSORT criteria for episodic or long-term use on day 90, the study assessment was performed at this time point to ensure patients were captured at the earliest stages of episodic or long-term use. The status of opioid use in these patients was monitored every month by reviewing the EHR. This approach to follow-up limits the time interval between establishment of CONSORT criteria for episodic or long-term use and the final study assessment.

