**Figure 2 figure2:**
[figure not shown]
Flow diagram for establishing Consortium to Study Opioid Risks and Trends (CONSORT) criteria for opioid use.

A randomly selected group of patients meeting criteria for short-term use at day 90 were invited to participate in the study assessment. This group of patients was selected to be time-matched 1:1 to patients continuing to use opioids at day 90 (initial issue date ±2 weeks) Although it was not possible to accurately apply CONSORT criteria for short-term use until month 6 following issuance of the last prescription, the study assessment was performed at this time point to ensure that patients were captured in the earliest stages of short-term use. Because it was anticipated that the majority of the cohort would meet criteria for short-term use, it was not feasible to invite all patients to participate in the study assessment.

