#### Data Analysis Plan

The primary research question for specific aim 1 was to identify patient characteristics associated with UPOU. A case-control design was used with controls time matched to cases. The expectation was that multiple patient characteristics would be associated with UPOU. Descriptive statistics (means, medians, and ranges) were generated to compare cases and controls on all patient characteristics. Differences in patient characteristics between cases and controls were assessed using bivariate tests including the McNemar test for categorical variables and paired 2-tailed *t* tests (or Wilcoxon signed rank test, if needed) for continuous variables. The results of the bivariate analyses were used to select variables for conditional logistic regression analyses to regress UPOU on all variables identified as potentially associated with the UPOU. The regression models were constructed in stages by incorporating predictors in conceptual blocks and using standard selection methods to retain variables. All models included a fixed effect for site. ORs and 95% CI were used to evaluate the magnitude and statistical significance of the association between predictors and outcome.

### Specific Aim 2

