#### SEM Analysis

The primary goal of aim 3 was to combine the results from aims 1 and 2 and extend these by building a statistical model that synergistically integrated the three domains of the UPOU conceptual framework. The UPOU framework has a number of complexities that limit the use of regression including multiple correlated predictors and outcomes, unobserved constructs that are difficult to directly measure, and nesting of patients with clinicians who are nested within sites. SEM can estimate latent variables and include them as both exogenous and endogenous variables in the same model, use multiple observable and quantifiable indicators to estimate latent variables from the shared variability of these indicators, and accommodate multiple endogenous variables (ie, dependent variables or outcomes) in 1 model. Multilevel SEM can estimate latent variables at 1 or more levels (eg, patient and clinician levels) and appropriately test associations at and across these different levels for categorical and continuous outcomes.

The SEMs were developed in several steps. The number of measurement models were estimated for all constructs that potentially used latent variables. Descriptive statistics were examined including means, medians, SDs, ranges, measures of central tendencies, and normality of the distributions. Extensive preliminary analyses were conducted to evaluate possible inconsistencies in the data, outliers, and variations in the data, and clinically and statistically relevant cutoff points that may facilitate the analyses were identified. The primary outcome measure was UPOU, measured as a dichotomous variable of cases and time-matched controls. The predictors of interest were grouped into 3 domains: patient characteristics, practice environment, and clinician characteristics. Each of these domains contained a number of directly observable and directly unobservable constructs. Examples of directly observable variables in the patient characteristic domain included age, sex, and employment status. Examples of directly unobservable constructs in the patient characteristic domain included symptoms of opioid withdrawal, opioid craving, and the psychosocial impact of chronic pain. Analyses (eg, coefficient α, principal components analysis, and factor analysis) were conducted to determine how to optimally combine scale items into reliable measures.

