### Limitations

The timeline of the research project was disrupted by the COVID-19 pandemic, but data collection was facilitated by no-cost extensions and leveraging the rural catchment area of Mayo Clinic. This produced an imbalance in the number of patients and clinicians recruited between the 3 clinical sites. While the overall target sample size was largely attained and therefore target statistical power was met, the imbalance potentially limited generalizability and precludes site-specific analyses for Yale University and University of Michigan. The opioid use status of cases and controls were based on the number of prescriptions issued by clinicians. As a result, discrepancies could exist between the number of prescriptions issued compared with the number of prescriptions dispensed by pharmacies. Finally, the CONSORT criteria were adapted to categorize opioid use 3 months following the initial prescription. Although it is possible that the status of opioid use could change over time, all patients were followed an additional 6 months to assess the stability of the opioid use category in cases and controls.

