### Conclusions

Following completion of data analysis, the study results will be immediately available for widespread dissemination in clinical practice and for use in ongoing research projects. It is anticipated that EHR systems will be leveraged to identify at risk patients receiving an initial opioid prescription and to send alert messages to members of the care team. This preemptive approach could also be used to develop direct-to-patient educational materials to raise awareness of the risk factors for developing UPOU.

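### Craving, withdrawal and opioid-difficulty measures are placed no earlier than month 3, after the groups were selected on day-90 opioid use, yet they stand as predictors or candidate predictors of UPOU

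*Protocol article*

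**What the plan says.** On timing, Study Assessments states: "Assessments were performed at 2 time points: 3 months following dispensing of the initial opioid prescription and 9 months following dispensing".

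On selection of cases, the section on the CONSORT timeline states: "Patients who continued to use opioids on day 90 following issuance of the initial opioid prescription were invited to participate in the study assessment". On controls, the text below Figure 2 states: "A randomly selected group of patients meeting criteria for short-term use at day 90 were invited to participate in the study assessment". The timeline section qualifies the status at that point: "Although it was not possible to accurately apply CONSORT criteria for episodic or long-term use on day 90". Limitations confirms that "the CONSORT criteria were adapted to categorize opioid use 3 months following the initial prescription".

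On the role of the measures, SEM Analysis makes UPOU the outcome and lists patient characteristics as one of three predictor domains. It adds: "Examples of directly unobservable constructs in the patient characteristic domain included symptoms of opioid withdrawal, opioid craving, and the psychosocial impact of chronic pain". The Aim 1 Data Analysis Plan compares cases and controls on all patient characteristics, then uses the bivariate results to choose variables for conditional logistic regression, so as to "regress UPOU on all variables identified as potentially associated with the UPOU". Predictors enter in conceptual blocks, with selection to retain variables. In the SEM, a saturated patient-level model is trimmed towards the fewest parameters that explain UPOU best.

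On use of the results, Conclusions anticipates that "EHR systems will be leveraged to identify at risk patients receiving an initial opioid prescription".

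**The concern.** A group selected for still taking opioids is compared with a group selected as short-term users, on symptoms and problems of taking opioids. Several instruments presuppose current or recent use. One craving item asks about the next dose. The Prescribed Opioid Difficulties Scale concerns problems tied to prescribed opioids. The article says the heat-pain device has been used to quantify opioid-induced hyperalgesia.

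A difference between the groups on such measures is partly built in by the selection, whether or not the measure helped to bring about prolonged use. A selection rule that rewards explanatory strength with few parameters favours these markers over weaker true antecedents. Two things are at stake: the reading of such measures as factors that facilitate UPOU, and any later tool for use at the initial prescription, when month-3 values do not exist.

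**Working it through.** **Step 1: time order, from the text.**

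| Item | When | Source |
|---|---|---|
| Initial prescription | day 0 | CONSORT timeline section |
| Groups selected by current opioid use | day 90 | CONSORT timeline section and text below Figure 2 |
| Craving, withdrawal, difficulties scale, mood, pain, heat pain | months 3 and 9 | Study Assessments |
| Check that the use category is stable | 6 further months | Limitations |

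Nothing in the article places the craving, withdrawal or difficulties instruments before month 3. The further 6 months test whether the category holds; they do not put the month-3 measures ahead of the selection.

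**Step 2: the plan's own figure.** The Aim 1 sample size section gives a detectable odds ratio (OR) of 1.38 with 600 cases and 600 controls, two-sided alpha 0.05, power 0.80, control prevalence 0.5 and r = 0. With the matched-pairs formula and P = OR/(1 + OR) = 1.38/2.38 = 0.580:

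- discordant pairs = (1.96/2 + 0.842 × √[P(1 − P)])² / (P − 0.5)² = 305.5
- probability of discordance = 0.580 × 0.5 + 0.5 × 0.420 = 0.50
- pairs = 305.5/0.50 = 611, close to 600

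Solving for exactly 600 pairs gives OR 1.384. The other two stated values also reproduce: 1.475 (stated 1.48) and 1.548 (stated 1.55). The power calculation is sound and is not the problem.

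**Step 3: how easily would a pure consequence of use pass the screen?** The documents give no prevalences, so the values below are assumptions. Take a marker with no influence on UPOU whose prevalence is p0 in controls and p1 in cases, the rise being due only to current use. Then

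- OR = p1(1 − p0) / [p0(1 − p1)]
- power = Φ{[|p1 − p0|√n − 1.96√(2p̄(1 − p̄))] / √[p1(1 − p1) + p0(1 − p0)]}, with p̄ = (p0 + p1)/2

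Example, 5% to 10%, n = 513 (the cases recruited; 517 controls): OR = 0.10 × 0.95/(0.05 × 0.90) = 2.11. The power term is (1.132 − 0.730)/0.371 = 1.085, and Φ(1.085) = 0.86.

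| Controls → cases | OR | Power, 600 per group | Power, 513 per group |
|---|---|---|---|
| 5% → 10% | 2.11 | 0.91 | 0.86 |
| 10% → 20% | 2.25 | >0.99 | >0.99 |
| 20% → 30% | 1.71 | 0.98 | 0.96 |
| 50% → 60% | 1.50 | 0.94 | 0.90 |
| 10% → 15% | 1.59 | 0.75 | 0.68 |
| 20% → 25% | 1.33 | 0.55 | 0.48 |
| 50% → 55% | 1.22 | 0.41 | 0.36 |

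Craving is scored 0 to 100, so a continuous version is also relevant. With power = Φ(d√(n/2) − 1.96), a use-induced shift of d = 0.2 SD has power 0.93 (n = 600) or 0.89 (n = 513), and 0.3 SD exceeds 0.99 at both sizes. These calculations treat the groups as unmatched; the matched analysis would differ somewhat with the within-pair correlation.

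**The case against.** The strongest reply is that formal UPOU status does not exist at month 3. The article says so, explains that early assessment was meant to catch patients at the earliest stages, and follows them for 6 more months. Craving or withdrawal at month 3 might help to sustain later use. That is fair: only a working status exists on day 90. But the difference in current opioid use exists then, and it drives the contrast. Time order holds only for later status among day-90 users.

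Other parts of the reply also stand and limit the point:

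- A reader might infer that nothing at all was collected at the initial prescription. The documents do not support this: Ethical Considerations mentions a paid initial screening whose content is not described, and one section refers to baseline smoking status.
- A reader might infer that every variable that differs enters the final regression. The plan builds models in blocks with selection, so the screen supplies candidates only.
- Only withdrawal and craving are named as predictor constructs. The difficulties scale enters by inference from the Aim 1 screen. The urine result is less certain: its stated role is to verify opioid status, although the Aim 1 text also lists biochemical confirmation among the framework elements.
- A reader might infer that the SEM paths are reversed. The article lets theory guide the direction of association, so this is not shown. It does not, however, move these constructs out of the predictor domain.
- The alert is an anticipated use, and nothing says that craving or withdrawal would drive it.
- Current mood and catastrophizing were measured deliberately, because past psychiatric diagnoses are imprecise. This argues against confining the whole primary analysis to pre-prescription variables.

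That case-control studies always measure after the outcome is a weaker reply. It serves for exposures that predate the outcome, such as age or past history, but withdrawal and craving are current states.

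**Conclusion.** The concern holds for measures that depend on current opioid use. They are first placed at month 3, after selection on day-90 use, and they stand as predictors (withdrawal, craving) or candidate predictors (difficulties scale, possibly the urine result) of UPOU. Part of any association follows from the case definition.

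The size cannot be taken from the documents. Under the assumed rises, consequences of moderate size (5% to 10%, 10% to 20%, 20% to 30%) give a spurious OR of about 1.7 to 2.3 and would usually pass the screen, with power of at least 0.86 at 513 per group. Rises of 5 points from 10%, 20% or 50% give an OR of about 1.2 to 1.6 and would pass less reliably, with power of 0.41 to 0.75 at 600 per group. A reader might assume a much rarer marker and obtain a far larger OR. Nothing in the documents supports such a figure, and the planned 1.38 would be the wrong yardstick, because it applies at 50% control prevalence.

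It would also go too far to say that these associations are wholly artefact, or that the demographic and history items are affected.

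**What to change.** 1. Remove craving, withdrawal, the Prescribed Opioid Difficulties Scale and the urine result as predictors of UPOU in the Aim 1 regression and in the SEM. Report them as concurrent correlates of opioid use, or use them only to predict month-9 status among day-90 users.
2. Label the other month-3 state measures (pain, depressive symptoms, catastrophizing, psychosocial function, heat pain) as concurrent.
3. Add a model limited to characteristics that predate the initial prescription, such as demographics and past medical and surgical history.
4. Base any statement about identifying at-risk patients at the initial prescription on that antecedent model.

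The cost is one more model set and changes to the analysis and manuscript wording; no new data are needed. The article reports that the Aim 1 analysis is complete with its manuscript in preparation, and that the SEMs are still in development, so the change can be made before publication. The downside is that fewer variables can be called risk factors.

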#### Demographics and Clinical Characteristics

Demographic and clinical characteristics were assessed including age, sex, ethnicity, marital status, education, employment status, BMI, and past medical and surgical histories including chronic pain.

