#### Mayo Clinic

Olmsted County residents who previously consented to have their medical records used for research purposes were identified using the Rochester Epidemiology Project (REP) medical records linkage system [7,8]. The REP provides access to all medical records for Olmsted County residents. The indications for opioid use in these patients were both surgical and nonsurgical pain. Patients recruited from this site reflected the characteristics of UPOU as it developed in a geographically defined population.

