#### Study Assessment

Clinicians were assessed using the Clinicians’ Attitudes and Beliefs About Opioids Survey (CAOS) [6]. The validity and test-retest reliability of the CAOS has been reported [6]. The CAOS also assesses clinician demographics and practice characteristics including sex, age, years in practice, professional training (physician surgeon, nonsurgeon physician, nurse practitioner, and physician’s assistant), organization of practice (single specialty, partnership, solo, or multispecialty), practice structure (academic or university versus clinic or hospital based), proportion of weekly patient appointments involving management of chronic pain, and proportion of patients with chronic noncancer pain currently receiving opioids.

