Many of the concepts to be tested with clinical data were approximated using administrative claims data. Diagnostic codes were used to measure comorbidities including depression, anxiety and substance use disorders. Procedure and diagnostic codes were used to infer pain etiology from surgery, trauma, and other causes. Place of service and clinician specialty codes were used along with prescription fill information to determine the source of opioid prescriptions. Patient geographic information and prescription fill information were used to determine regulations governing the use of prescription drug monitoring programs.

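### The surgical or nonsurgical reason for the initial opioid is not matched on, not named as a measure and not forced into any model, so patient and especially prescriber associations with UPOU may be confounded by indication

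*Protocol article*

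**What the plan says.** All references are to the protocol article.

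- **Measures.** *Demographics and Clinical Characteristics*: "Demographic and clinical characteristics were assessed including age, sex, ethnicity", continuing to BMI and past medical and surgical histories. The list is worded as open. The measures described after it, from opioid verification to concomitant treatments, do not name the reason for the index prescription.
- **Matching.** *Timeline for Establishing CONSORT Criteria*: "This group of patients was selected to be time-matched 1:1 to patients continuing to use opioids at day 90", within two weeks of the initial issue date. The Aim 1 *Data Analysis Plan* repeats this: "A case-control design was used with controls time matched to cases". No other matching factor appears.
- **Modelling.** Aim 1 *Data Analysis Plan*: "The results of the bivariate analyses were used to select variables for conditional logistic regression analyses", followed by staged entry in blocks with variable selection. A site effect is in every model. Aim 2 uses the same approach, and the variables it describes screening are clinician and practice characteristics.
- **Case mix.** *Mayo Clinic*: "The indications for opioid use in these patients were both surgical and nonsurgical pain". Yale is described in the same way. The University of Michigan is surgical only.
- **Prescriber type.** Aim 2 *Study Assessment* records "professional training (physician surgeon, nonsurgeon physician, nurse practitioner" and physician's assistant.
- **Claims data.** *National Administrative Claims Database Analysis*: "Procedure and diagnostic codes were used to infer pain etiology from surgery, trauma, and other causes".

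**The concern.** UPOU is defined as opioid use that outlasts the expected resolution of acute pain. That expected period plausibly depends on why the opioid was given, and so do the kind of patient and the kind of prescriber. A variable related to both predictor and outcome, and absent from matching and model, can produce an association where there is no effect.

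Aim 2 is most exposed. Surgeons will presumably write mostly for surgical pain, so surgeon versus nonsurgeon may largely mark the indication. The Discussion expects the models to separate the influence of patient, clinician and practice domains, and to lead to clinician education and record-system alerts. That attribution needs indication to be held constant.

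**Working it through.** **1. The plan's own benchmark.** The Aim 1 sample-size section gives a detectable odds ratio (OR) of 1.38 for 600 pairs, control prevalence 0.5, no within-pair correlation, two-sided α 0.05 and 80% power. With discordant fraction d and π = OR/(1+OR), power = Φ{[√(600d)(π−0.5) − 1.96×0.5]/√(π(1−π))}. At OR 1.38, d = 0.5 and π = 0.580, which gives 79.3%. Solving for 80% gives 1.384. The other two stated values also reproduce (1.47 against 1.48; 1.55 against 1.55). The sample-size figures are not at fault.

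**2. Can site stand in for indication?** From *Patient Recruitment*, the two mixed sites supplied (855 + 147)/1030 = 97.3% of patients. The planned share was 1560/2340, or two thirds. In Aim 2, 146 of 148 clinicians (98.6%) came from Mayo Clinic, so the site term is nearly constant. Site removes almost none of the surgical/nonsurgical difference.

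**3. Size under assumed values.** The documents give no rates by indication, so every input here is an assumption. Half of the initial prescriptions are taken as surgical. Scenario A has UPOU in 15% of surgical and 40% of nonsurgical patients (average 27.5%). Scenario B has 20% and 30% (average 25%). These averages are close to the planning rate of 20% + 7% = 27% and to the 25% cited in the Introduction. Date matching is taken as unrelated to indication, so the matched OR equals the marginal one. The predictor has no effect within either indication.

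Nonsurgical share:
- A: cases 0.40/0.55 = 0.727; controls 0.60/1.45 = 0.414.
- B: cases 0.30/0.50 = 0.600; controls 0.70/1.50 = 0.467.

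| Predictor with no effect | Prevalence, surgical / nonsurgical | Cases | Controls | Spurious OR |
|---|---|---|---|---|
| Patient exposure, A | 20% / 40% | 0.345 | 0.283 | 1.34 |
| Patient exposure, B | 20% / 30% | 0.260 | 0.247 | 1.07 |
| Surgeon prescriber, A | 90% / 5% | 0.282 | 0.548 | 0.32 |
| Surgeon prescriber, B | 90% / 5% | 0.390 | 0.503 | 0.63 |

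**4. Cross-check by external adjustment.** Spurious OR = (a·K + 1 − a)/(b·K + 1 − b). Here a and b are the shares with the higher-risk indication among exposed and unexposed controls, and K is the indication–UPOU odds ratio.

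| a / b | K = 1.5 | K = 2 | K = 3 |
|---|---|---|---|
| 60% / 40% | 1.08 | 1.14 | 1.22 |
| 70% / 30% | 1.17 | 1.31 | 1.50 |
| 90% / 10% | 1.38 | 1.73 | 2.33 |

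The result is exactly 1.00 if a = b or K = 1. In this grid the bias reaches 1.38 only under strong imbalance.

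**5. Precision cost for the surgeon term.** With the 90%/5% split at 50:50, surgeon prevalence is 0.475 and the covariance with indication is 0.45 − 0.5×0.475 = 0.2125. The correlation is 0.2125/√(0.25×0.475×0.525) = 0.85. Variance inflation is 1/(1 − 0.851²) ≈ 3.6, so the standard error grows by about √3.6 = 1.9. This is a linear approximation to the logistic model.

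**The case against.** **The article is condensed and its list is open.** Absence from that list does not show that indication went unrecorded. This stands. A reader might infer that the study never collected it, and the documents do not support that. Records were reviewed throughout. Surgery in the six months before the index prescription was an exclusion, and histories were taken at 3 and 9 months. A recent operation reported at month 3 would therefore be the index operation or a later one, so indication is largely recoverable.

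**The claims model may not differ from the clinical one.** A reader might take the use of pain etiology in the claims data as a mismatch. The article introduces the claims variables as approximations of concepts tested with clinical data and calls the claims model similar, so a mismatch is not shown.

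**Screening might catch it.** If indication was recorded and offered to the Aim 1 screen, it would pass clearly under scenario A (73% of cases against 41% of controls nonsurgical). That is fair, but nothing in the text puts it in the Aim 1 pool or protects it from the later selection steps. The Aim 2 screen is described for clinician and practice characteristics only.

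**The comparison with 1.38 is loose.** That value applies at control prevalence 0.5. At the 0.283 of scenario A, the detectable OR for 600 pairs is about 1.41. This stands, and 1.38 is used here only as an order of magnitude.

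**The aims ask about association, and the data are in.** The article reports the Aim 1 and Aim 2 analyses as complete, so an added adjustment comes after the fact. This bears on how the adjustment is labelled. It does not remove the need for it, because the Discussion reads the associations as domain influences.

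**Conclusion.** The point holds as a risk that the stated analysis does not control. Indication is not a matching factor, not a named measure and not a forced term, and site cannot replace it. A reader might go further and say that the reported associations are confounded. The documents do not support that, because they give neither the link between indication and UPOU nor the link between indication and any predictor.

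Under the assumptions shown, the effect on a patient predictor runs from negligible (OR 1.07) to close to the effects the study was sized for (1.34), and is nil for predictors unrelated to indication. For surgeon versus nonsurgeon it could be large (0.63 to 0.32). That rests on an assumed 90%/5% split, and the article does not say for which indications nurse practitioners and physician's assistants prescribe. The change is worth making, most of all for Aim 2.

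**What to change.** State whether the index indication was recorded. If it was not, derive it from the electronic records and surgical histories already under review. Use categories aligned with the claims-data etiology (surgery, trauma, other). Keep it, with site, in every Aim 1 and Aim 2 model and in the structural equation models, exempt from bivariate screening and from model trimming.

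Because the Aim 1 and Aim 2 analyses are reported as complete, label the adjustment as added and show results with and without it. The structural equation models are still in development and can include it from the start.

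The cost is one abstracted covariate. Precision loss should be small for most patient predictors, but it would be wrong to expect that for the surgeon term. There the variance could rise about 3.6-fold under the 90%/5% assumption, with only 148 responding clinicians. If the data cannot separate surgeon from indication, report that and do not interpret the surgeon association as a clinician effect.
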